**Summary**

Access to the best available evidence, and the ability to obtain and understand such information is seen as necessary to protect the public’sinterests and critical to empowerment, but is also a precondition for participation in the decision making.

A web portal serving as a generic (non disease- specific) tailored tool was developed in the conceptual framework of shared decision making and evidence based practice to improve the lay- public’s critical and social literacy skills and activation. A randomized controlled parallel trial using a simple randomization procedure will be conducted, including 200 parents of children <4 with internet access. Parents will be allocated to receive either the portal or no intervention. Primary and secondary outcomes include: the ability to find research based information, critical appraisal skills, perceived behavioural control, attitudes and perceived pressure associated with searching for information, and participation.

**Introduction**

Access to the best available evidence, and the ability to obtain and understand such information is seen as necessary to protect the public’sinterests and critical to empowerment, but is also a precondition for participation in the decision making . The importance of health literacy has been argued and is often defined as “the degree to which individuals have the capacity to obtain, process, and understand basic health information and services needed to make appropriate health decisions”. In a review of the evidence, health literacy was found to be a stronger predictor of health status than age, income, employment status, education level and ethnicity . Health literacy and participation in health decisions has been associated with improved health outcomes and cost effectiveness but is also advocated on ethical grounds by facilitating equal access to healthcare respecting user autonomy .

Based on pre-studies and a literature search we identified three main barriers to obtain, process, and understand health information; the ability to interpret health information, knowing where to find reliable and relevant information and being able to obtain information in consultations. These barriers will be sought addressed by improving patients’ critical appraisal skills, improving access to reliable sources of health information and providing a checklist for exchange of health information to be used in consultations with health professionals. This will be done using a web portal serving as a generic (non disease- specific) tailored tool developed in the conceptual framework of shared decision making and evidence based practice.

Consumer health informatics is a branch of patient directed interventions that aims to reach patients directly trough new information and communications technologies in an interactive way . In an review of the available evidence and based on a number of reviews and controlled trials, Coulter and colleague found that interventions using new information technologies may improve knowledge, demonstrate high user satisfaction and positive effects on self-efficacy and health behaviour . Evidence also point to that web based patient directed interventions may have benefits over that of conventional means of relaying information

When evaluating the intervention we wanted to focus on a specific health issue in order to contextualize the portal. The case that has been chosen for this trial is childhood vaccinations. The reasons for this are several. Few, if none, are so much in contact with health providers and have questions about how to treat and prevent health problems as parents of small children (49). Childhood vaccinations are voluntary in Norway, and thus this is a health decision that concerns all parents. Moreover, childhood vaccinations is an interesting case considering it has been a hot topic of discussion in the media during the last few years, and many strong and often conflicting opinions have been expressed in the public debate suggesting both important health effects as well as severe side effects .

**Overview of the trial**

*Design*

The trial will done using a parallel design where each group of participants is exposed to only one study intervention.  One group will receive access to the portal and its tools, the other group (control group) will receive no treatment.

**The research question**

What are the effects of patient directed web-portal to improve health literacy skills.

| **P** | Parents of children age <4 |
| --- | --- |
| **I** | Portal |
| **C** | No treatment/ practice as usual |
| **O** | The ability to find research based information, critical appraisal skills, perceived behavioural control, attitudes and perceived pressure associated with searching for information, and participation. |
| **T** | Primary objective:  -Is the portal more likely to improve actual and perceived self- efficacy associated with searching for health information and critical appraisal skills compared to no treatment/ practice as usual?  Secondary objectives:  -Is the portal more likely to improve participation (searching behaviour and activation) compared to no treatment/ practice as usual?  -Is the portal more likely to increase the perceived pressure to search for health information? |

**Trial population**

*Trial site(s) and population(s)*

Parents of children age <4 will be recruited with access to internet.

Considering that the portal primarily is targeted at people who already are searching for information on their own, the intervention will only be relevant for those who already have access to internet. Search for health information has been found to be negatively correlated with age and positively with education . In the Norwegian population<16 years, 2/3 have attained a tertiary education and nearly all households with children have internet at home .

Allowing for that the portal can be used in relations with a health visit, we will limit our sample to include parents of children <4. At this age children are still following the vaccination program but are also on average in contact with a health provider 3 times per year, decreasing with age up to early adolescence where the trend changes back again (49). At the time where parents have children <4, they are also in a peak when it comes to health visits themselves, with a mean number of health visits 4,6 contacts each year (49).

*Exclusion criteria*

Participants will be excluded if one other in the household already participates in the study (due to spill-over effect) and if they do not have children <4. Since the recruitment will be done online, there is no need to screen for access to internet.

*Sources or methods of recruitment*

We wish to recruit participants where they search for information. Thus, participants will be recruited at the maternity and child health centers and through social media and internet sites.

A pamphlet and an ad will be developed based on the participant information material that has been approved by the Norwegian Social Science Data Services (NSD) and Regional Committees for Medical and Health Research Ethics (REK). The pamphlet will be distributed through the maternity and child health centers, whereas online communities and internet sites will be contacted and asked for permission to publish the ad.

The inclusion/ exclusion for study participation will be done online where possible participants will be asked to answer a short online screening form. They will also receive information about the study and asked to consent to participation.

If the participant does not meet the inclusion criterion, he or she will be given an automated feedback describing that they are not eligible to participate in the study.

Those that meet the inclusion criteria will be randomized to receive the intervention or no intervention.

Recruiting

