**Allocation of interventions**

*Methods for randomisation and stratification*

Simple randomization procedure using SPSS will be used.

Recruitment rate will be observable through Questback.

The participants will be sequential allocated.

*Methods for concealment of allocation*

Allocation concealment has been described *as “the process that prevents any trial participant or investigator from knowing in advance the treatment to which subjects will be assigned”* . In order to prevent selection bias participants who meet the inclusion criteria will be allocated based on an automated system. The participants will not be informed about which study group they are allocated to.

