**Post-recruitment retention strategies**

*Participant retention*

- Basic non-sensitive background information and email-addresses will be kept on file.
- Two reminders are planned per activity if participants fail to respond.

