**Sample size**

*Sample size justification*

The intervention is considered to be passive and the effect sizes are expected to be conservative. A pragmatic power-analysis was conducted based on the primary outcome measure, considering a minimum detectable difference in means of 1,0 (standard deviation of 2.1) and based on continuous outcome measure results in 70 participants in each group (total n=140). It is recommended that the sample size is inflated to allow for any loss to follow up; leaving the sample size for this trial to be effectively around 200.

*Missing data*

No efforts will be made to impute missing data. All analyses will be performed on available cases, but based on the intention to treat principle (all participants analysed in the group they were randomised to).

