**Analysis strategies**

All data will be entered into SPSS and analysed by [name] under the advice of a statistician [name].

- Searching ability

The outcome will be evaluated pragmatically by categorizing the information as based on: 1. research or 2. expert advice/ other. The information will be categorized blindly by two independent researchers. The direction of effect is expected to be positive, in that more participants will find research based information than those in the control group. The hypothesis will be tested using Relative Risks with corresponding confidence intervals.

- Critical appraisal skills (DISCERN)

The mean value rating of the information will be measured against a “standard” rating made by experts on the same information. Two hypothesis regarding critical appraisal skills will be tested:

1. The direction of effect is predicted to be positive, in that the mean overall score of the intervention group will be closer to the standard than the control group. To this end the absolute difference between the “standard rating” and the rating made by each participant will be calculated.
2. It is also expected that the scored overall quality will be lower for the intervention group since studies have found that people using explicit criteria as a base for evaluation tend to be more critical .

Both hypotheses will be tested using one-sided T-tests.

- Satisfaction with the portal

Satisfaction scales measuring the domains on 1- 7. Each domain will be summarised using mean, standard deviation, median and Inter Quartile range.

-Self-efficacy, attitudes and perceived pressure associated with searching for information (the theory of planned behaviour)

For each of the sub-domians attitude, subjective norm and perceived behavioural control of TPB-questionnaire a (weighted) composite score(see attachment for further information) will be calculated. The direction of effect is expected to be positive, in that improvements will be seen in sub-domains perceived behavioral control and attitudes, but may also be seen in increased perceived pressure. This will be t-tested using T-tests (two-sided).

An item analysis (Crohnbach’s alpha) exploring internal consistency within each composite score relating to the direct measures will be conducted. The TPB manual estimates that an acceptable internal consistency co-efficients should be approximately >0.6.

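### No group comparison adjusts for a baseline covariate, although the protocol names age and education as correlates of searching: prespecified adjustment would be a cheap, modest improvement, not the repair of an error

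*Protocol*

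**What the plan says.** - Trial population, on who looks for information: "Search for health information has been found to be negatively correlated with age and positively with education". The strength of these correlations is not given. The same section says of a Norwegian reference population that "2/3 have attained a tertiary education".
- Allocation of interventions: "Simple randomization procedure using SPSS will be used". The subheading mentions stratification, but no factor is named.
- Figure 2 and Data collection and management place the search exercise, the DISCERN rating, and the Theory of Planned Behaviour (TPB) and patient activation (PAM) questionnaires in weeks 1, 2 and 3, all after allocation. No outcome has a baseline value.
- Analysis strategies, for searching ability: "The hypothesis will be tested using Relative Risks with corresponding confidence intervals". The two DISCERN hypotheses get one-sided t-tests. The TPB sub-domains and PAM get two-sided t-tests. None of these has a covariate.
- The only multivariable model in that section regresses intention on group, the TPB composite scores and their interactions with group.
- Post-recruitment retention strategies: "Basic non-sensitive background information and email-addresses will be kept on file". The variables are not listed.

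**The concern.** With no stratification and no baseline outcome score, demographic variables are the only prognostic information this trial could use, and the protocol names two of them. Leaving both out has two possible costs. First, variance that age and education could explain stays in the error term, in a trial that expects modest effects from a passive intervention. Second, if the arms happen to differ in education or age, the estimate carries that difference. An adjustment added after the imbalance has been seen is open to the charge of being chosen from the data.

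The intention regression does not fill the gap. Its composite scores are collected in week 3 and may themselves be changed by the portal, so they cannot stand in for baseline covariates.

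**Working it through.** **Inputs.** From Sample size: target difference 1.0, SD 2.1, 70 per group (140 in total), raised to about 200 for losses. From Trial population: proportion tertiary educated 2/3. Assumed, because the protocol does not give them: two-sided alpha 0.05 and 80% power, and R², the share of outcome variance explained by age and education, from 0.02 to 0.20.

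**1. The plan's own figure.** n per group = 2 × (1.960 + 0.842)² × 2.1² / 1.0² = 69.2, rounded up to 70. The stated size reproduces without any covariate, and 140 / 0.70 = 200 corresponds to 30% loss. Nothing in this point disturbs the sample size.

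**2. Continuous outcomes.** Adjustment reduces the residual SD to 2.1 × √(1 − R²). Putting that into the same formula gives:

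| Assumed R² | Residual SD | SE relative to unadjusted | n per group for 80% power | Power at 70 per group |
|---|---|---|---|---|
| 0 (unadjusted) | 2.100 | 1.000 | 70 | 80.4% |
| 0.02 | 2.079 | 0.990 | 68 | 81.2% |
| 0.05 | 2.047 | 0.975 | 66 | 82.4% |
| 0.10 | 1.992 | 0.949 | 63 | 84.4% |
| 0.20 | 1.878 | 0.894 | 56 | 88.3% |

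At 100 per group, power is 92.0% unadjusted, 92.5% at R² 0.02 and 96.4% at R² 0.20. These power figures are for a two-sided test. The DISCERN tests are one-sided, so for them only the SE column carries over.

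**3. Chance imbalance in education.** Under simple randomisation with roughly equal arms, the SE of the between-arm difference in proportions is √[(2/3)(1/3)(4/N)].

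- N = 200: SE = 0.0667. A gap above 0.10 is 1.50 SE, with two-sided probability 13%. The 95% range is ±13.1 points.
- N = 140: SE = 0.0797. A gap above 0.10 is 1.25 SE, with probability 21%. The 95% range is ±15.6 points.

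**4. What such a gap could do to a mean difference.** If education alone explained a share R² of the variance, its coefficient would be 2.1 × √(R² / (2/9)): 0.996 at R² 0.05 and 1.992 at R² 0.20. Multiplied by a gap at the 95% limit with 70 per group (0.156), the shift in the estimate is 0.16 to 0.31, against a target difference of 1.0. With 100 per group it is 0.13 to 0.26.

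**5. The search relative risk.** The variance formula in step 2 belongs to the linear model and does not carry over to a binary outcome analysed by relative risk. No precision gain is claimed there.

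**The case against.** The strongest reply is that nothing planned is invalid. After simple randomisation, an unadjusted relative risk or t-test is unbiased on average, and its error rate and confidence interval already allow for chance imbalance. A reader might infer from the absence of covariates that the comparisons are biased or that the trial is underpowered. The protocol supports neither reading. This part of the objection stands, with one qualification: the guarantee applies to everyone randomised, whereas the protocol analyses available cases without imputation. Adjustment for age and education would also relax the assumption about dropout somewhat.

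A second reply is that the key sentence describes who searches for health information. It does not say that age or education predicts whether a pasted link is research based, a DISCERN rating, a TPB score or PAM. A reader might take the two variables as established predictors of the trial outcomes, and the documents do not go that far. The inference is short for the search and TPB outcomes, which concern searching, and weaker for DISCERN and PAM.

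Third, the inputs are soft. R² has no source in the protocol. Recruiting parents of young children where they look for information may narrow the spread of both variables, which makes the upper end of the range harder to defend. The two-thirds figure describes a national population, not the recruits. If 85% were tertiary educated (an assumption), the chance of a gap above 10 points would fall to about 10% at N = 140 and 5% at N = 200. Nor does the protocol say that 140 parents are expected to complete: 140 is the calculated requirement, and no loss rate is stated. These points limit the size of the gain but do not remove it.

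Finally, a statistical analysis plan that is not shown might add adjusted analyses. That is possible, but the protocol itself names the test for each outcome, and none includes a baseline term.

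**Conclusion.** The point holds as a modest improvement. No between-group comparison in Analysis strategies adjusts for a baseline covariate, in a trial with simple randomisation, no baseline outcome measures and two candidate covariates named in its own text. For the continuous outcomes the gain runs from under 1 to about 8 percentage points of power at 70 per group, over an assumed R² of 0.02 to 0.20, and is probably towards the lower end. For the relative risk the case rests on protection against chance imbalance, which matters only to the extent that education or age predicts the outcome. It would go too far to say that all the analyses lack further terms, since the intention regression has them; what is missing is any baseline term.

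**What to change.** In Analysis strategies, prespecify the group comparisons as adjusted for age and education:

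- linear regression on group, age and education for the DISCERN, TPB and PAM scores, in place of the t-tests;
- modified Poisson regression with robust standard errors for the search outcome, so that the result is still a relative risk;
- the unadjusted results shown alongside in every case.

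State how age and education will be coded. If either is not among the background data already kept, add it to the online screening form, so that it is recorded before randomisation and is available for everyone randomised.

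The cost is a few lines of analysis text, slightly more analysis work and at most two extra items on an existing form. If the covariates turn out to be unrelated to the outcomes, little is lost: entered as one term each, they use 2 of the 138 residual degrees of freedom available with 140 analysed.

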**Action:**

Screening for inclusion using Questback + informed consent

If not meeting inclusion criteria- exclusion

**Action:**

Email explaining reason for exclusion

If meeting inclusion criteria-

Inclusion in study

**Action:**

Participants randomised and sequentially assigned to study groups

*Figure 1- recruiting procedure and allocation procedure*

**Allocation of interventions**

*Methods for randomisation and stratification*

Simple randomization procedure using SPSS will be used.

Recruitment rate will be observable through Questback.

The participants will be sequential allocated.

*Methods for concealment of allocation*

Allocation concealment has been described *as “the process that prevents any trial participant or investigator from knowing in advance the treatment to which subjects will be assigned”* . In order to prevent selection bias participants who meet the inclusion criteria will be allocated based on an automated system. The participants will not be informed about which study group they are allocated to.

**Simple**

**randomisation**

**Portal**

**Week 1:**

Searching exercise

**No intervention**

**Week 1:**

Searching exercise

**Week 2:**

Critical appraisal of health information (Questback)

**Week 2**:

Critical appraisal of health information (Questback)

**Week 3:**

Final questionnaires

(Questback)

**Week 3:**

Final questionnaires

(Questback)

*Figure 2- study design*

**The interventions**

*Description of intervention*

The intervention target for this evaluation was developed as a tailored intervention where pre- studies, a literature search and process evaluation studies helped tailor the content and design as it is today. The portal was tailored to improve the lay public’s’ “healthy skepticism”, or in other words, critical and social literacy skills to assist patients in the decision-making process and for improving access to health information and participation. Illustrated by typical examples which can be found in the news and through patient stories, the portal provides an introduction to research methods, the underlying principles of science and critical assessment tools appropriate for a lay public. Framing and how to disseminate health information is complex. By using scenarios, real-life examples and plain-language terms , the portal focuses on *how* research is conducted, and *why* this is important, rather than just reporting conclusions and expert interpretations. In essence, the portal includes three sections.
1. A checklist for critical assessment of health information
2. Access to research databases for health information and an introduction to research methods and principles of science

3. A checklist to the consultation

The portal was not designed as an online course since this was considered to be a tedious and unlikely approach to take by many users. Instead, an important principle has been that the division of topics should be logically structured for those who want to navigate through menus, but users should also be able to “play” their way through the content by clicking on the titles that look interesting sparking interest. The portal was intended to target the public in general and those who are interested in health information, but also as a suitable tool to be used in the consultation. Generic and applicable to all health decisions, the portal and its included tools will be freely available of no cost, to be accessed online, downloaded or printed out in a user friendly format.

*Intervention delivery*

With the exemption of the first welcoming letter, the intervention will be delivered online, and all responses will be recorded using Questback. At three different stages the participants will be sent an email containing a task.

Each task corresponds with the three main categories of content that the intervention (portal) aims to target; improved search, improved critical appraisal skills and improved activation.

A week interlude has been allowed between each task. This choice of timing was based on two pragmatic considerations; allowing for that the participants may use one week to complete the task at their own pace and time, and at the same time considering the potential consequences on the response rate and participation fatigue that a longer follow-up may have.

*Contact*

With the exemption of the first initial information letter, all communication will take place using email and Questback.

